**Table 1 T1:**
[figure not shown]
Time points and content of on-site data collection.

#### Symptom scoring

2.5.1

Patients were required to fill out a questionnaire, including TCM syndrome scores and symptom survey with the 12 Ocular Surface Disease Index (OSDI) items.^[26]^

#### Eye examination

2.5.2

Schirmer I tests (without anesthesia): performed by placing a strip in the unanesthetized eye over the lower lid margin, midway between the middle and outer third and recording the length of the strip that was wetted after 5 minutes.

The noninvasive tear film break-up time (NITBUT): NITBUT measurements are evaluated using the Keratograph 5 M (OCULUS Optikgeräte GmbH, Wetzlar, Germany). The professional operator will note the first NITBUT (NITBUTf), and the average value of the intervals after blinking on the corneal viewing area are recorded as the average NITBUT (NITBUTav).

Meibomian gland loss: Images showing Meibomian gland loss of the right upper eyelid were obtained using the OCULUS Keratograph ocular surface analyzer in accordance with the manufacturer's instructions. Analyze and record the ratio of meibomian gland dropout area to the total area.

Fluorescein staining: Corneal-conjunctiva staining was accessed using the cobalt-blue filter of the slit-lamp light source through a Wratten 12 yellow filter, 2 minutes after instilling 5 mL of 2% sodium fluorescein. The eye is divided into three equal compartments: the cornea, the nasal conjunctiva and the temporal conjunctiva. The staining of each region is graded from 0 to 3 points. A score of 0 represented no staining; a score of 1 represented 1-30 staining dots; a score of 2 scores represented > 30 staining dots; a score of 3 scores represented total staining with ulcer and filaments. The final stain scores are the sum of the ranks of the three regions.

#### Safety indicator

2.5.3

Laboratory tests including blood routine and urine routine, liver and kidney function, blood lipids, 12-lead ECG, electrocardiogram, etc. and blood pressure, respiration, heart rate, and body temperature are measured before and after the study. Any adverse events or adverse reactions related to the treatment method or drugs are observed, and the study will be terminated if necessary.

#### Safety assessment

2.5.4

During the entire study period, any adverse events will be documented and reported in detail. Protocols have also been designed to support researchers in situations where participants becomes distressed or presents with risks to self or others.

### Sample size

2.6

In an N-1 design that is repeated between participants, the size of the sample (series) is not based on the ability to test group effects using inferential statistics. And the examinations for each individual trial may change over time, allowing us to use predefined criteria to determine if treatment is effective for each subject. In this study, we selected 12 samples (N trials, 12 replicates) with at least four measurement points per cycle. This sample size will be sufficient to provide information on whether the intervention is applicable to the individual to examine the direction of the “average therapeutic effect” between individuals and to provide an estimate of the variability of intra- and inter-individual outcomes in that population. As a standard for the N-of-1 trial, this number of participants will allow for statistical analysis of the magnitude of the effect of the intervention relative to the baseline.

### Randomization and blinding

2.7

A total of 40 sets of random numbers are generated by www.randomizer.org. Every odd number is designated as the individualized treatment prescription and even number is designated as the control prescription (placebo). The random orders of the two treatment formulations are allocated by opaque envelope. We estimate to recruit 12 participants in the feasibility study and use 36 sets. Other 4 sets are spare. The test drugs were randomly assigned by the database administrator according to the coding table. The prepared research drugs will be delivered, stored, and distributed in the pharmacy of Ineye Hospital affiliated to Chengdu University of TCM. Both the drugs have no differences in appearance, dosage form, color, specification, and so forth. Due to the special nature of TCM treatment, double-blind cannot be achieved. The patients, data managers and outcome assessors will be blinded during the trial.

### Adherence to study medication

2.8

Study drug compliance will be assessed by:

(1)weekly self-recorded drug intakes;(2)the trial staff will ask questions about compliance during the planned telephone consultation from the first week after the start of the review and(3)The number of drug bags returned after the treatment is completed. At the end of the treatment period, participants will be asked to return all unused medication for counting in a reply-paid post satchel.

### Data collection and management

2.9

The trial will set up the project Executive Committee (EC), Monitor Group (MG) and Data and Safety Monitoring Group (DSMG). All the data is obtained from the research medical record, which is flled in by the researcher. The data is collected through the electronic case report form (e-CRF) that must be completed for each selected case. Create a dedicated database for data entry and management and the data manager is responsible for data management. Data entry is done by trained personnel and performs data quality and accuracy checks. Two data administrators should perform 2 separate inputs and proofreading to ensure the accuracy of the data.

### Quality assurance and data integrity

2.10

The trial will be conducted in accordance with the protocol, the ICH Good Clinical Practice Guide and all relevant local ethical regulations. Data collection will be performed in accordance with the pre-approved protocols, and the quality of the study will be managed by regular monitoring-MG. The integrity of the test data will be monitored by periodically checking for omissions and errors in the data sheet.

### Statistical analysis

2.11

All data analyses are performed using SAS. A population estimate of effect by aggregating individual N-of-1 results was used. The results of all complete cycles were combined to produce a posterior probability of the overall difference between TCM individualized treatment cycles and placebo cycles. For all analyses, *P* *<* .05 is considered statistically significant.

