**Methods::**

This trial is a single-case randomized, single-blind, placebo-controlled study. A total of 12 subjects will be recruited in this trial. The trial is divided into three cycles, and one cycle has 2 treatment periods. There is a washout period at each adjacent treatment stage. TCM individualized treatment and placebo will be randomized during the treatment period. The test period will last for 29 weeks, with 4 weeks for each treatment period and 1 week for each washout period to minimize carryover effects. Subjects will be selected by the researcher strictly in accordance with the inclusion and exclusion criteria. The outcomes will evaluate the efficacy of treatment by changes in the various observation indicators.

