### Trial design

2.1

This is a single-case randomized controlled single-blind study. The study population comes from Ineye Hospital affiliated to Chengdu University of Traditional Chinese Medicine. Twelve subjects will be screened for diabetes with DED. The single participant who met the inclusion criteria of TCM clinical response underwent 3 cycles of treatment periods with 6 observation periods, 2 of which are in one cycle, including 4 weeks of TCM individualized treatment and 4 weeks of placebo. In each cycle of testing, each subject determines the order in which the two drugs are used simulant at random. All participants will continue their basic treatment during entire the trial period. There is no washout period at the beginning of the study and there is 1 week washout period at each adjacent treatment stage to make carryover effects minimized and observe the disease development.

The study will be conducted in October and November, 2019. The intervention will begin in November and December 2019 and it is planned to be concluded by September and October, 2019. The entire study experiment time is 29 weeks. Figure 1 shows the overall flow of the subject's drug treatment process. The protocol is compliant with the Standard Protocol Items: CONSORT extension for reporting N-of-1 trials (CENT) 2015.^[20]^ If the symptoms change and develop, patients will be offered the option of stopping a treatment period early and waiting for the other treatment period after a washout period or withdrawing the trial.

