#### Withdrawal criteria

2.3.4

Participants who meet any of the following conditions will be removed from the study:

(a)Patients with poor compliance who did not take drugs according to requirements of the study protocol were rejected;(b)voluntary withdrawal from the trial;(c)intolerant or allergic to the drug.

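### Pooling only complete cycles, when periods may be stopped for symptoms and patients removed after randomisation, can bias the TCM-placebo difference in either direction

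*Protocol article*

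**What the plan says.** Three parts of the protocol article bear on this.

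- **Section 2.11 (Statistical analysis)** sets what enters the population estimate: "The results of all complete cycles were combined to produce a posterior probability of the overall difference" between TCM and placebo cycles. It names no other pooled set and does not say what makes a cycle complete.
- **Section 2.1 (Trial design)** ties early stopping to symptoms: "If the symptoms change and develop, patients will be offered the option of stopping a treatment period early". The patient then waits for the other treatment after a washout, or withdraws from the trial.
- **Section 2.3.4 (Withdrawal criteria)** takes participants out of the study after randomisation. One criterion reads "Patients with poor compliance who did not take drugs according to requirements of the study protocol were rejected"; another covers those "intolerant or allergic to the drug"; the third is voluntary withdrawal.

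The scale is small. The abstract states "A total of 12 subjects will be recruited in this trial" and "The trial is divided into three cycles, and one cycle has 2 treatment periods". Section 2.7 allots 36 randomisation sets to them.

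**The concern.** Treatment order is randomised within each cycle, so the TCM-placebo contrast is protected only as long as cycles enter the analysis for reasons unrelated to treatment and outcome. A stop triggered by a change in symptoms is related to outcome, and removal for intolerance is related to the drug. If such events decide which cycles are pooled, the remaining cycles are those in which both periods went tolerably, and the comparison is no longer the randomised one.

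The direction depends on which treatment loses more of its bad periods. If TCM works, placebo periods are stopped more often, the worst placebo values disappear, and the benefit is diluted. If TCM causes intolerance and the worse TCM periods are lost, the benefit is inflated. Section 2.7 does not list the treating doctor among those blinded, so stopping could differ by treatment even without a true effect. The posterior probability carries whatever bias results, and with at most 36 cycles the lost information also matters.

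**Working it through.** **The plan's own figures.** 12 participants × 3 cycles = 36 cycles, which matches the 36 sets in section 2.7. 6 × 4 + 5 × 1 = 29 weeks, which matches the stated duration. The article gives no SD, effect size, stopping rate or dropout rate, so everything below rests on assumptions.

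**Illustration 1: symptom-driven stopping under a real benefit.** Assumptions: higher score is worse; within-patient SD per period is 1; the placebo mean is 0 and the TCM mean is −d with d = 0.5; a period stops when its score exceeds c; a cycle with any stopped period is dropped.

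- Share stopped: placebo 1 − Φ(c), TCM 1 − Φ(c + d).
- Mean of retained placebo periods: −φ(c)/Φ(c).
- Mean of retained TCM periods: −d − φ(c + d)/Φ(c + d).
- Benefit in complete cycles: d + φ(c + d)/Φ(c + d) − φ(c)/Φ(c).
- Cycles lost: 1 − Φ(c)Φ(c + d).

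For c = 1:

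- Stopped: placebo 1 − 0.841 = 16%, TCM 1 − 0.933 = 7%.
- Placebo mean −0.242/0.841 = −0.288; TCM mean −0.5 − 0.130/0.933 = −0.639.
- Benefit 0.639 − 0.288 = 0.351 against a true 0.50, about 30% too small.
- Cycles lost 1 − 0.841 × 0.933 = 21%, leaving about 28 of 36.

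| c (SD) | Placebo stopped | TCM stopped | Benefit (true 0.50) | Shortfall | Cycles lost |
|---|---|---|---|---|---|
| 0.5 | 31% | 16% | 0.5 + 0.288 − 0.509 = 0.278 | 44% | 42% |
| 1.0 | 16% | 7% | 0.5 + 0.139 − 0.288 = 0.351 | 30% | 21% |
| 1.5 | 7% | 2% | 0.5 + 0.055 − 0.139 = 0.416 | 17% | 9% |

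A simulation of 20,000 trials of 12 × 3 cycles agrees. With a true difference of −0.5, the complete-cycle estimate is −0.43, −0.39, −0.33 and −0.28 when 5%, 10%, 20% and 30% of placebo periods stop, with about 34, 31, 26 and 21 cycles left.

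**Illustration 2: no true effect, same stopping rule for both treatments.** The simulated bias is 0.00 at every stopping rate tried, although only about 33 to 18 cycles remain. Complete-cycle selection therefore costs precision here but does not bias.

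**Illustration 3: no true effect, extra stops on TCM.** Let the symptom rule stop 10% of periods on either treatment (threshold 1.282, where φ = 0.175). In addition, let each TCM period worse than the TCM average stop with probability t. The mean of retained TCM periods is [−φ(0) + (1 − t)(φ(0) − 0.175)] / [0.5 + 0.4(1 − t)], with φ(0) = 0.399. The retained placebo mean is −0.175/0.9 = −0.195.

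- t = 10%: −0.230 − (−0.195) = −0.035
- t = 20%: −0.269 − (−0.195) = −0.074
- t = 40%: −0.358 − (−0.195) = −0.163

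These are false benefits for TCM. The simulation gives the same to within rounding (−0.03, −0.07, −0.16).

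**The case against.** Several points on the other side stand and limit the claim.

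- **Complete is undefined.** Section 2.1 says "patients will be offered the option of stopping a treatment period early and waiting for the other treatment period after a washout period" is on offer, so a cycle with a shortened period may still contain both treatments and may be meant to count. The figures above hold only if it does not. On the other reading, early stopping removes fewer cycles; cycles cut short by the removals in section 2.3.4 are still left out.
- **A reader might infer that the difference is biased.** The documents do not support that: with no effect and equal stopping the bias is zero, and a change in symptoms is not said to mean worsening, though that is the natural reading.
- **A reader might infer that the value at an early stop is never recorded.** Section 2.5 lists the planned visits but does not exclude an assessment at a stop, and Table 1 is not shown.
- **A reader might infer that all data from removed patients are discarded.** Section 2.3.4 does not say so. Section 2.11, read literally, keeps cycles completed before removal. Nor does the text say that poor compliance depends on treatment.
- **Bitter taste is no documented reason for more stops on TCM.** Section 2.4 describes a placebo with a bittering agent and a taste basically consistent with the test drug.

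It may also be said that this is called a feasibility study and is not sized for a group test (sections 2.6 and 2.7). That lowers the stakes, but section 2.11 still promises a population estimate. That a separate analysis plan may add detail does not answer the point, because the article itself states the complete-cycle set.

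**Conclusion.** The concern holds in conditional form. The article states a complete-cycle rule for its only described pooled analysis, alongside symptom-triggered stopping and removals after randomisation. If a stopped period makes its cycle incomplete, the pooled TCM-placebo difference can be biased whenever stopping or removal differs by treatment. The bias runs toward zero if a real benefit causes more stops on placebo: 0.35 instead of 0.50 SD in the central illustration, 0.28 to 0.42 over the thresholds tried. It favours TCM if worse TCM periods are lost: about 0.03 to 0.16 SD under no effect. All these sizes depend on assumed effects, thresholds and stopping rates. The direction in this trial cannot be known from the document.

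**What to change.** **Section 2.11.** Replace the complete-cycle sentence with wording such as: all randomised periods with an outcome value are analysed under the treatment randomised for that period, whether or not the cycle is complete and whatever the compliance, in one mixed or Bayesian hierarchical model. Define a complete cycle and report that analysis as a sensitivity analysis.

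**Section 2.3.4.** State that data collected before removal are kept, and continue scheduled assessments of poor compliers who consent.

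**Early stops.** Record the end-of-period assessments at the stop and use them in the main analysis. Add a sensitivity analysis on how that value is handled, because exposure is shorter and the reading may be taken at a flare. The simulation returned the true difference with all cycles kept, but only on the assumption that the stop value equals what the full period would have given.

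**Cost.** Wording in two sections, an assessment at each early stop, and a little more analysis work. The main estimate then describes periods as randomised, with mixed exposure lengths, rather than completed pairs; this should be stated. No extra patients are needed, and the clinical option to stop is unchanged.

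### Section 2.11 applies P < .05 to every analysis while section 2.5 lists seven efficacy measures with none primary; tested once each, they carry up to about a 30% chance of at least one false positive

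*Protocol article*

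**What the plan says.** The testing rule is in section 2.11: "For all analyses, *P* *<* .05 is considered statistically significant". Nothing in that section ranks the outcomes, adjusts for their number or marks any of them as exploratory.

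The outcomes to which the rule applies are in two subsections of 2.5:

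- Symptom scoring (2.5.1) has a questionnaire "including TCM syndrome scores and symptom survey with the 12 Ocular Surface Disease Index (OSDI) items", which gives two measures.
- Eye examination (2.5.2) adds five: Schirmer I, first NITBUT, average NITBUT, meibomian gland loss ("Analyze and record the ratio of meibomian gland dropout area to the total area") and fluorescein staining ("The final stain scores are the sum of the ranks of the three regions").

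The text shown does not name a primary outcome. The Methods part of the abstract says only that "The outcomes will evaluate the efficacy of treatment by changes in the various observation indicators". The Objective part of the abstract points to clinical symptoms and long-term efficacy. The Discussion part of the abstract points to objective eye measures and systemic symptoms, and the main Discussion to a range of objective measures. These statements do not converge on one outcome.

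**The concern.** A threshold of .05 limits the false-positive risk of one test. Used unchanged on seven efficacy measures of equal standing, it leaves a much larger risk that at least one crosses the line by chance. The abstract says that the trial should supply evidence that TCM works on eye measures and systemic symptoms. With 12 patients and no designated primary outcome, nothing in the text prevents an isolated significant result from being presented as that evidence, and a reader would have no rule for discounting it.

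This is more than a detail left to an analysis plan. The article itself fixes the threshold and extends it to all analyses. A later plan that adjusted the tests, or withheld significance claims from some of them, would depart from that sentence.

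**Working it through.** **Inputs from the protocol article**

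- Threshold per analysis: .05 (section 2.11).
- Efficacy measures: 2 (section 2.5.1) + 5 (section 2.5.2) = 7, or 6 if first and average NITBUT count as one.
- The article states no overall error rate, so there is no figure of its own to reproduce.

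**Assumptions, not in the article**

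- One pooled TCM-versus-placebo test per measure.
- Two-sided tests; sidedness is not stated.
- No true effect on any measure.
- Pairwise correlations between test statistics of 0 to 0.9. The article gives none, so a range is shown.

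**Step 1. Any false positive, independent tests**

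- Seven measures: 1 − 0.95^7 = 0.302, which is 0.302 / 0.05 = 6.0 times the per-test level.
- Six measures: 1 − 0.95^6 = 0.265.
- Ceiling under any dependence: 7 × 0.05 = 0.35.

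**Step 2. False positive in favour of TCM only**

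Each two-sided .05 test has a 0.025 chance of erring in TCM's favour. For seven independent tests, 1 − 0.975^7 = 0.162. The comparator is 0.025, not 0.05.

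**Step 3. Correlated tests**

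Simulation of seven normal test statistics with a common correlation, 1,000,000 draws, critical value 1.96:

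| Correlation | Any false positive | In favour of TCM |
|---|---|---|
| 0 | 30% | 16% |
| 0.3 | 27% | 14% |
| 0.5 | 23% | 11% |
| 0.7 | 18% | 9% |
| 0.9 | 11% | 6% |

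For two-sided normal tests, independence gives the largest value and correlation lowers it. If only the two NITBUT summaries are correlated (0.9) and the rest are independent, the result is 28%.

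**Step 4. After a fix**

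One primary outcome tested at .05 has a false-positive chance of 5%. If all seven stayed confirmatory, a Bonferroni threshold would be 0.05 / 7 = 0.0071 per test, giving 1 − (1 − 0.00714)^7 = 4.9% under independence.

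**The case against.** The strongest reply is that this is a condensed article. Outcome hierarchy and multiplicity are commonly left to an analysis plan that is not shown, and the content of Table 1 is also not shown. That would answer a complaint about silence. It does not fully answer a written rule that covers all analyses. A later plan could still name a primary outcome without contradicting the article, which is one reason why the repair is easy.

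Several parts of the reply stand:

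- **No overall rate is claimed.** A reader might infer that the article presents 5% as the error rate of the whole trial. It does not; it states a threshold per analysis.
- **One win is not declared sufficient.** A reader might infer that any single significant measure would establish efficacy. No sentence says so, and judging by various indicators could also mean weighing them together.
- **Seven P values are assumed.** Section 2.11 describes a posterior probability for the overall difference, not a P value per outcome. How that fits with a P < .05 rule is a separate question.
- **Independence is the extreme case.** Both NITBUT summaries come from the same measurement, and the TCM syndrome criteria include eye dryness and grittiness, which plausibly overlap with OSDI.
- **The framing is modest.** Section 2.6 says that the sample was not sized for inferential testing of group effects, and section 2.7 calls the work a feasibility study.

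It might also be argued that only errors favouring TCM matter, so that 16% should be set against 5%. That comparison is wrong: the nominal rate in that direction is 2.5%, so the inflation is about 6.5-fold under independence (0.162 / 0.025).

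**Conclusion.** The point holds at moderate severity. Applied as written to seven unranked efficacy measures, the rule in section 2.11 gives about a 30% chance of at least one false positive under independence (26% with six measures) and 18% to 27% at assumed correlations of 0.7 to 0.3. In favour of TCM alone it is up to about 16%, against a nominal 2.5%. These figures rest on one pooled two-sided test per measure and no true effect. The correlations are assumptions, and the six-fold inflation belongs to the independent case only.

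A reader might go further and apply the rule within each patient, giving 7 × 12 = 84 tests and 84 × 0.05 = 4.2 expected false positives. The article does not support that count. Section 2.6 refers to predefined criteria for judging each subject but does not say that they are P values.

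The feasibility label and the absence of inferential sizing keep this below a must-fix. They also make a blanket significance rule harder to justify.

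**What to change.** Before unblinding:

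1. Name one primary outcome, with its time point, that matches the stated objective. OSDI is one candidate because the objective refers to symptoms. It is not the only one, since the abstract also targets objective eye measures; the sponsor should choose.
2. Reword section 2.11 so that the .05 rule applies to that outcome alone.
3. Report the remaining measures as secondary, with interval estimates and either Holm-adjusted P values or no significance claim.
4. Keep only one NITBUT summary in any tested set and report the other descriptively.

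The cost is a change of wording in the protocol and the registry entry. No added patients, visits or measurements are needed. The sponsor gives up the option of calling nominal wins on secondary measures significant.
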